### Patient identification and enrollment

4.6

#### Source of participants

4.6.1

The participants will be recruited through the outpatient and inpatient departments of the Teaching Hospital of Chengdu University of TCM, Mianyang Hospital of TCM, and Shuangliu Hospital of TCM. We will also include 40 cases of Teaching Hospital of Chengdu University of TCM, 10 cases of Mianyang Hospital of TCM and 10 cases of Shuangliu Hospital of TCM.

#### Diagnostic criteria

4.6.2

(1) Western medicine diagnosis and classification criteria for diabetes: the criteria recommended in the 1999 WHO expert consultation report.^[13]^

Diagnostic criteria: Patients conforming to one of the following conditions can be diagnosed

Symptoms of diabetes + plasma glucose level at any time ≥11.1 mmol/L (200 mg/dL)Fasting plasma glucose (FPG) level ≥7.0 mmol/L (126 mg/dL)In the glucose tolerance test, the plasma glucose level at 2 h is ≥11.1 mmol/L (200 mg/dL)

Classification criteria:

Type 1 diabetesType 2 diabetesOther typing (omitted)

Patients who meet one of the conditions can be diagnosed with diabetes. This study targeted patients with type 2 diabetes and excluded those with type 1, gestational, and other special variations of diabetes.

(2) Lower extremity atherosclerosis diagnostic criteria: “Specifications for the screening and management of lower extremity arterial disease in patients with type 2 diabetes” issued by the Chinese Medical Association Diabetes Branch in 2013. Imaging basis: according to the color Doppler ultrasound images, the measured lower extremity blood vessels include the common iliac artery, external iliac artery, superficial femoral artery, iliac artery, anterior tibial artery, peroneal artery, posterior tibial artery, and dorsal foot artery. Lower extremity atherosclerosis is considered if the medial thickening of the wall of any blood vessels ≥1 mm, it is not smooth, atherosclerotic plaques are present, or the local lumen of the artery is narrowed or even completely occluded. Detection of lower limb IMT: <1.0 mm is considered normal, 1.0 to 1.2 mm is considered mildly thickened, >1.2 mm is considered to be an atheromatous plaque formation, while the presence of a normal and mild thickening suggests the absence of an atheromatous plaque, subsequently leading to the diagnosis of lower extremity atherosclerosis.^[14]^

(3) TCM syndrome diagnostic criteria for diabetic Qi-yin deficiency and blood stasis syndrome: according to the “ Guidelines for clinical research of new Chinese medicines.”^[15]^

Main symptoms: dry mouth, dry throat, fatigue, numbness, or tingling in the limbsSecondary symptoms: shortness of breath and words, hot hands and feet, constipation, yellow urineTongue image: red and dry, dark color with blood stasis, sublingual veins are darkPulse: weak, thin and fast, or blocked or string1.Diagnosis can be made considering the tongue and pulse.2.It can be diagnosed with the presence of dry mouth and throat, fatigue in combination with dark ecchymosis of the tongue or bruising purple veins or astringent pulses.

#### Inclusion criteria

4.6.3

Participants are considered eligible for the study if they meet the following criteria:

1.Voluntarily participation in the trial with signature on the informed consent form;2.Aged 35 to 65 years;3.Diagnosis of Western medicine type 2 diabetes and TCM syndrome, and diabetic macrovascular complications

#### Exclusion criteria

4.6.4

1.Patients with heart and kidney dysfunction, acute coronary syndrome, cerebrovascular accident, hematopoietic disorders, and mental illness;2.Patients with acute metabolic disorders such as diabetic ketoacidosis within the past 1 month;3.Pregnant or lactating women;4.Severe infection in the past 1 month;5.Patients with allergic constitution;6.Uncooperative in run-in period;7.Having a history of alcoholism or drug abuse

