#### Rejection criteria

4.6.5

1.Those who do not to meet either the inclusion or exclusion criteria after enrollment;2.Those who have not used the medicines according to the regulations, cannot judge the curative effect or provide incomplete information;3.Those who have consumed drugs that are forbidden and may influence the judgment of effection;4.Those who have acute infection during the test

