#### Secondary outcomes

4.8.2

1.Measurement of blood glucose levels before three meals, 2 h after three meals, and before sleeping; calculation of average blood glucose levels (MBG), standard deviation of mean blood glucose (SDBG), and maximum blood glucose fluctuation (LAGE).2.β-cell function evaluation index: insulin resistance index (HOMA-IR), area under the glucose curve (SG), and area under the C-peptide curve (SCP). Calculating HOMA-IR, SG, and SCP by:Homa-IR (CP) = 1.5 + G 0 min × CP 0 min/2800; Homa-islet (CP) = 0.27 × CP 0 min/(G 0 min − 3.5);SG = (G 0 min + G 180 min)/2 + G 30 min + G 60 min + G 120 min;SCP = (CP 0 min + CP 180 min)/2 + CP 30 min + CP 60 min + CP 120 min;(G 0 min to G 180 min, CP 0 min to CP 180 min, respectively means blood glucose and C-peptide values at each time point after Steamed bun test).^[18,19]^Blood glucose will be tested at visits 1, 3, and 5. β-cell function evaluation index will be tested at visits 1 and 5.3.Blood lipid: total cholesterol (TC), triglyceride (TG), high density lipoprotein cholesterol (HDL-C), and low density lipoprotein cholesterol (LDL-C);4.Inflammation indicators (NLR, IL-6, and CRP)5.HbA1c

Blood glucose will be tested at visits 1, 3, and 5. β-cell function evaluation index, HbA1c, inflammation indicators and blood lipid will be tested at visits 1 and 5.

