#### Statistical analysis method

4.9.8

We will use the SPSS20.0 software for statistical analysis of the experimental data. Measurement data will be tested by *t* test, expressing as mean ± standard deviation. Paired design *t* test may also be used for intra-group comparisons. The chi-square test will be used for the enumeration data. Rank-sum test will be used for rank data. The comparison of survival rate and survival time between the two groups will be analyzed by Kaplan–Meier curve.

The analysis data set will be selected from the following:

1.Full analysis set (FAS): Including all subjects who received at least one treatment after randomization and having more than one follow-up record. If the case fails to complete the treatment course, the final observation should be implemented instead. The number of subjects who will undergo evaluation for the efficacy at the end point should be the similar to that at the beginning of the trial.2.Per protocol (PP): In accordance with the treatment protocol, the main variables can be determined, and there is no major violation of the experimental protocol.3.Statistical analysis of the main variables: Analyze the data of the full analysis set and the matching plan set.

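### The infection rules at entry and after enrolment do not match, so a patient with a current non-severe infection can be randomised, sampled for inflammation markers, and then meet a rejection ground

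*Protocol article*

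**What the plan says.** The exclusion criteria (4.6.4) deal with infection in one item, "Severe infection in the past 1 month". No other inclusion or exclusion criterion bars a current infection that is not severe.

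The rejection criteria (4.6.5) apply after enrolment. The fourth is "Those who have acute infection during the test", with no grade attached. The first, "Those who do not to meet either the inclusion or exclusion criteria after enrollment", does not reach the patient considered here, because that patient satisfies the entry criteria as written.

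The secondary outcomes (4.8.2) include NLR, IL-6 and CRP, and "inflammation indicators and blood lipid will be tested at visits 1 and 5". Each marker therefore has one baseline and one later value.

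The statistical analysis section (4.9.8) allows that a paired t "test may also be used for intra-group comparisons". It defines the full analysis set as "Including all subjects who received at least one treatment after randomization", with a follow-up requirement, and substitutes the final observation for patients who do not complete the course. The per-protocol set requires that "there is no major violation of the experimental protocol". Neither definition says what happens to a rejected case. Section 4.6.7 says only that dropouts are analysed.

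**The concern.** The rejection rule treats acute infection as a reason to remove a patient, but the entry rule does not apply the same standard. Someone with a minor acute infection can pass 4.6.4, be randomised, give visit 1 blood, and fall under 4.6.5 if the infection is still present once the trial is under way.

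Two things are at stake. One is avoidable loss of randomised patients from a small trial. The other is the quality of the baseline for CRP, IL-6 and NLR, which any acute infection can raise and which have no second baseline measurement. The setting makes this plausible: recruitment includes inpatients (4.6.1), and lowering low-grade inflammation is part of the trial's rationale (abstract and section 3).

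**Working it through.** The plan gives no figure on this point to reproduce: no infection frequency, no CRP, IL-6 or NLR values, and no definition of acute or severe infection. Its only design calculation, the sample size, concerns SDBG and has no bearing here.

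**Step 1: the two rules side by side.**

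| Infection at enrolment | 4.6.4 (entry) | 4.6.5 (after enrolment) |
|---|---|---|
| Severe, within the past month | excluded | not reached |
| Acute, not severe, current | admitted | rejectable if it persists into the trial |

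The second row is the gap.

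**Step 2: what can happen to that patient.**

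- *Rejected and removed from the analysis.* The raised baseline leaves with the patient and a paired test has no pair. There is no spurious fall, but one randomised patient is lost: 1/30 = 3.3% of an arm.
- *Stops early but stays in the full analysis set.* The final-observation rule applies. With markers taken only at visits 1 and 5, the value carried forward is that of visit 1, so the change is zero. A raised value then stands in for visit 5 and adds noise.
- *Kept, infection resolves, completes visit 5.* The baseline may be raised and visit 5 is not. Only this path yields a fall without any treatment effect.

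**Step 3: illustrative size of the third path.** All inputs are assumptions except the 30 per arm: no treatment effect; log-marker SD 1; correlation 0.5 between visits 1 and 5; a fraction f of patients infected at baseline; infection raises the log-marker by s = 1 or 2 SD, has resolved by visit 5, and the patient is not rejected.

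The expected within-group change is −f × s; for example, f = 0.20 and s = 2 give −0.40 SD. The variance of the change is 2(1 − 0.5) + f(1 − f)s² = 1 + f(1 − f)s²; at f = 0.20 and s = 2 this is 1 + 0.16 × 4 = 1.64, an SD of 1.28 in place of 1.

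Simulation with 8,000 trials per scenario and tests at the two-sided 5% level gave:

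| f | s | Mean within-group change (SD) | Paired t test rejects | Between-arm test of change rejects |
|---|---|---|---|---|
| 0 | – | about 0 | 5.0% | 5.0-5.2% |
| 5% | 1 | −0.052 | 5.7% | 4.7% |
| 5% | 2 | −0.101 | 7.1% | 4.8% |
| 10% | 1 | −0.099 | 8.3% | 5.0% |
| 10% | 2 | −0.200 | 13.6% | 4.8% |
| 20% | 1 | −0.195 | 15.8% | 5.2% |
| 20% | 2 | −0.398 | 36.0% | 4.9% |

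The between-arm difference in change was at most 0.008 SD in every scenario. A comparison of visit 5 values alone rejected in 4.6-5.2% of trials.

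**The case against.** The strongest reply is that the two rules do different jobs and need not match. The rejection item reads naturally as an infection that arises after the start. There is a two-week screening period in which an investigator may notice an infection, and a condensed article may leave the definitions of acute and severe to the full protocol. Part of this stands: the article does not say when the trial period begins for this rule, so whether a patient is rejectable on the day of entry is open. It does not close the gap. Both lists are printed, and nothing in them stops a patient with a current non-severe infection from being enrolled and sampled.

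A reader might go further and infer that baseline CRP, IL-6 and NLR are inflated relative to visit 5. The documents do not support that. Nothing shows that infected patients would be enrolled, or how many. The inference also needs patients infected at visit 1 to be kept while those infected later are removed, and no such rule is stated. As step 2 shows, removal takes the raised baseline away, and the final-observation rule gives zero change.

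A reader might also infer a biased treatment effect. With 1:1 randomisation, infections at baseline are balanced between arms in expectation, and the simulation shows no inflation of the between-arm error rate.

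**Conclusion.** The mismatch is real and the two sections should be reconciled, but it is a minor point. Its consequences are the possible loss of a randomised patient for a condition detectable at entry, added noise in three secondary markers, and a possible spurious fall in the within-group paired tests, which the plan makes optional. The between-arm comparison is not biased in expectation by this route, and the primary ultrasound outcome is not affected.

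The size cannot be determined from the article. The paired-test error rates of 6-7%, 8-14% and 16-36% at 5%, 10% and 20% infected depend on the assumed 1 to 2 SD shift, the assumed correlation of 0.5, and every infected patient being kept and recovered by visit 5. At the low end of that range the effect is close to nothing.

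**What to change.** Apply one standard in both sections. In 4.6.4, extend the infection item so that it also covers any acute infection present at visit 1, and state that visit 1 sampling and randomisation are deferred until the infection has resolved. The rejection item in 4.6.5 then applies only to infections that begin later.

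The change costs one clause and a short enrolment delay for the few patients affected. In return it keeps randomised patients in the trial and gives the inflammation markers a cleaner single baseline.

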## Research basis of Shenqi compound and its unique hypoglycemic advantages

3

Shenqi compound has been used in clinical settings for 16 years. It was initially mass produced internally in the Teaching Hospital of Chengdu University of TCM in 2016. It has been used in 19 medical institutions in 19 districts (cities), counties, and high-tech zones within Sichuan province. Currently, it has been included in the “Diabetic Clinical Diagnosis and Treatment Program” of the National TCM Clinical Research (Diabetes) Base.

Previous research by the research group has confirmed that Shenqi compound can regulate glucose and lipid metabolism disorders, improve vascular function, and effectively prevent and treat diabetic vascular disease.^[9]^ In 2015, the National Natural Science Foundation of China (No. 81503566)^[10]^ found that it can regulate serum insulin level, inhibit mTOR activation and autophagy, and regulate the circadian clock Id2 and Usp2 genes of the pancreatic tissue to stabilize blood glucose. Comprehensive evaluation, Shenqi compound has multiple effects of reducing blood glucose fluctuation, reduces low-level inflammation, protects blood vessels, subsequently providing a research basis for this subject.

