#### Traditional Chinese medicine intervention

4.5.3

All participants in the treatment group will visit the researchers once every month, when the same Chinese doctor will examine them using four TCM diagnostic methods including inspection, listening and smelling, inquiry, and pulse measurement and palpation. Shenqi compound is composed of 8 Chinese herbs: ginseng, astragalus, raw radix rehmanniae, trichosanthin, dogwood, yam, salvia, and wine rhubarb. Ginseng and astragalus supplement the vitality together as the remedy. The four medicines are used in cooperation with each other to supplement the deficiency of yin and jin of the lungs, spleens, and kidney. Salvia miltiorrhiza and wine rhubarb are used as adjuvants to promote blood circulation and remove blood stasis. Shenqi compound regulates the body's energy metabolism and reduces blood glucose fluctuation, which is a good recipe for clinical treatment of type 2 diabetes with lower extremity atherosclerosis. At present, it has been included in the “Diagnosis and Treatment Program for Diabetes” of the Chinese Traditional Medicine Clinical Research (Diabetes) Base. The test drug is a Chinese medicine formula granule produced by Sichuan Green Pharmaceutical Technology Development Co., Ltd. Certification and quality control by director of the department of pharmacy department in the Teaching hospital of Chengdu University of TCM. Usage instructions suggest consuming the granules three times a day one lattice each time, by boiling with water before meals, stirring, covering, and sealing for 3 to 5 min. The main ingredients of placebo are beta-cyclodextrin and artificial food colors. Shenqi compound and placebo are both fried-free granules, are similar in packaging, appearance, and shape. Participants are not allowed to take other drugs during the 8-week study period. Each participant will receive 28 boxes of Chinese medicine formula granules. Participants will be asked to record the changes in their symptoms daily using a form reviewed by a researcher once every month.

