#### Clinical examination

4.9.1

Before the start of the trial, a history of diabetes, current medication, other medical history, and treatment history will be recorded. The anthropometric data will be collected at five time points (baseline, w4, w8, w12, w24), will be collected using standardized inspection procedures including: gender, age, height (shoes removed), weight (after morning urine, fasting status), body mass index (BMI), waist circumference (perimeter of the horizontal plane at the midpoint of the axillary midline from the rib arch to the midpoint of the crotch margin), hip circumference (largest possible hip circumference), waist-to-hip ratio (WHR). Measure vital signs including blood pressure, heart rate, breathing, and temperature.

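### Eligibility neither bars nor washes out current or recent Shenqi users, although two thirds of patients come from the hospital where Shenqi was first mass produced

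*Protocol article*

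**What the plan says.** Section 3 describes a product already in circulation. On how long, it says: "Shenqi compound has been used in clinical settings for 16 years". Large-scale production is said to have begun at the Teaching Hospital in 2016. On how widely, the same section says: "It has been used in 19 medical institutions in 19 districts (cities), counties, and high-tech zones within Sichuan province". It adds that Shenqi is part of the treatment program of the national TCM diabetes research base.

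Section 4.6.1 recruits from the outpatient and inpatient departments of three hospitals, in the split "40 cases of Teaching Hospital of Chengdu University of TCM, 10 cases of Mianyang Hospital of TCM and 10 cases" at Shuangliu.

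Section 4.6.3 has three inclusion criteria: consent, age, and the diagnoses including the TCM syndrome. Section 4.6.4 has seven exclusion criteria, the last three being "Patients with allergic constitution;6.Uncooperative in run-in period;7.Having a history of alcoholism or drug abuse". Prior or current use of Shenqi, or of any Chinese medicine, appears in neither list.

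The timeline under section 4.7.1 gives 2 weeks of screening, 8 weeks of intervention and 24 weeks of follow-up. It does not call the screening period a washout. The run-in named in exclusion 6 is not described anywhere in the text. Section 4.5.3 forbids other drugs, but only during the 8-week study period. Section 4.9.1 states that "a history of diabetes, current medication, other medical history, and treatment history will be recorded" before the trial starts, with no consequence for eligibility.

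**The concern.** A patient who takes Shenqi up to the day before the trial meets every printed criterion and can be allocated to either arm. On Shenqi, such a patient simply continues and has little or nothing further to gain. On placebo, the same patient has to stop.

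The consequence depends on how long the earlier effect lasts. Where it lasts, as it might for the vessel wall, both arms already carry it and the treatment difference shrinks. Where it fades, as it might for glucose, lipids or inflammation markers, part of the observed difference is worsening after withdrawal and not improvement from adding the drug. In both cases the baseline is no longer an untreated one. That matters for the within-group paired t tests that section 4.9.8 allows.

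**Working it through.** **1. Can a current user be randomised?** Four places could prevent it:
- Inclusion criteria (4.6.3): no requirement to be free of Shenqi.
- Exclusion criteria (4.6.4): no item on Shenqi. Two other items do carry look-backs of one month (acute metabolic disorders, severe infection), so the list is written at a level of detail where such a rule would belong.
- Screening and run-in (4.7.1, exclusion 6): 2 weeks, no washout stated, run-in not described.
- Drug ban (4.5.3) and the rejection criterion on forbidden drugs (4.6.5): the ban covers the 8 weeks only, and the criterion comes without a list.

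None of them does, so the answer on the printed text is yes.

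**2. Recruitment share.** 40/60 = 66.7% from the Teaching Hospital.

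**3. The plan's own sample size, as a base for illustration.** Section 4.5.7 gives σ = 2.41 and δ = 2.0 for SDBG, with 1.64 and 1.28 for α = 0.05 and β = 0.1:

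n = 2 × [(1.64 + 1.28) × 2.41 / 2.0]² = 24.76 per arm, so 25 per arm and 50 in total. This reproduces the stated figure. The value 1.64 is one-sided, so the powers below are one-sided too.

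**4. Effect of prior users.** Let p be the share of prior users; the documents do not give it. Assume that each enters with the full effect δ and gains nothing more. Let f be the fraction of that effect still present at the end in a prior user on placebo.
- Expected change on Shenqi: −δ(1 − p).
- Expected change on placebo: +δp(1 − f).
- Expected between-arm difference in size: δ(1 − p) + δp(1 − f) = δ(1 − pf).

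With f = 1 (fully persistent) the difference is δ(1 − p). With f = 0 (fully reversible) it stays δ, of which a share p is withdrawal on placebo.

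Power = Φ(δ(1 − p) / (σ√(2/n)) − 1.645), normal approximation. For p = 0.2 and n = 25: 1.6 / (2.41 × √0.08) − 1.645 = 2.347 − 1.645 = 0.702, so 76%.

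| Assumed p | f = 1: difference | Power, 25 per arm | Power, 30 per arm | f = 0: change on Shenqi | f = 0: change on placebo | f = 0: difference |
|---|---|---|---|---|---|---|
| 0 | 2.0 | 90% | 94% | −2.0 | 0 | 2.0 |
| 0.1 | 1.8 | 84% | 89% | −1.8 | +0.2 | 2.0 |
| 0.2 | 1.6 | 76% | 82% | −1.6 | +0.4 | 2.0 |
| 0.3 | 1.4 | 66% | 73% | −1.4 | +0.6 | 2.0 |

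The proportional shrinkage (1 − p) applies to any persistent outcome under these assumptions. The powers do not carry over: they use the SDBG effect size, and glucose is more plausibly reversible. The primary Doppler outcome has no effect size in the documents.

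**The case against.** Section 3 reports that Shenqi was available, not how many candidates have taken it. The background regimen in section 4.4 lists acarbose, insulin detemir, antihypertensives and a lipid-lowering drug, with no sign that Shenqi users are expected. This stands: the harm is conditional on such patients enrolling.

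A reader might infer that the control arm is in fact partly a withdrawal arm, or that the trial no longer estimates the effect of adding Shenqi. The documents do not support either statement. Randomisation balances prior use in expectation, and for a fully reversible effect the between-arm difference is unchanged. A reader might also infer a definite loss of power, or that adverse events will be understated because prior users tolerate the drug. The first needs a prior-user share and a Doppler effect size that are not given, and the second has no basis in the text.

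Nor should the lead hospital be described as the maker of the trial drug. Section 3 says only that mass production began there, and section 4.5.3 states: "The test drug is a Chinese medicine formula granule produced by Sichuan Green Pharmaceutical Technology Development Co., Ltd". The exposure argument rests on earlier clinical use and is unaffected.

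Finally, the schedule figure is not shown, the run-in might serve as a washout, and a list of forbidden drugs may sit in a fuller protocol. That is possible. But the eligibility criteria are printed as complete numbered lists, and prior use of the test drug is an eligibility matter that those lists leave open.

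**Conclusion.** The point holds as an unguarded risk. Followed as printed, the plan can randomise current or recent users of the test drug, and it draws 67% of its patients from the hospital where that drug was first mass produced.

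If a share p of such patients enrols, the expected difference falls to (1 − p) of its value for outcomes where the earlier effect fully persists, and by less where it persists only in part. For reversible outcomes the difference is kept in expectation, but a share p of it is withdrawal, and baselines and paired within-group comparisons are distorted. These results assume that each prior user enters with the full effect and gains nothing more, which is the extreme case. The powers in the table are illustrations only.

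This is a cheap improvement, not a fatal flaw. Its weight depends on a share that only the sites can know.

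**What to change.** - Add to section 4.6.4 an exclusion for current or recent use of Shenqi compound in any form, with a look-back window that the investigators set and justify. Check it against the medication and treatment history already recorded under section 4.9.1.
- State what the run-in in exclusion 6 consists of, and whether it serves as a washout.
- Record any earlier use of Shenqi, and report a sensitivity analysis without earlier users.

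The cost is one criterion, one screening question and one extra analysis. Some candidates will be lost and recruitment may be slightly slower, mainly at the lead hospital. An exclusion window does not remove an effect that outlasts it, which is why the sensitivity analysis is needed as well.

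Separately, section 4.4 gives a 4-week treatment period, while section 4.5.3 and the timeline under section 4.7.1 give 8 weeks. These passages must be reconciled, and the look-back window should not be tied to the treatment period until they are.
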